**Fig. 1 Fig1:**
[figure not shown]
Study design. TIA, transient cerebral ischemia; IABP, intra-aortic balloon pump; ECMO, extracorporeal membrane oxygenation

Two hours after randomization, heparin (100 IU/kg) will be administered intravenously in 5 mL of 0.9% sodium chloride every 4 h in the heparin group. In the tirofiban group, tirofiban (0.05 g/kg/min) will be infused over 22 h using a micropump starting within 30 min of randomization. To maintain treatment blinding, a 5-mL volume of 0.9% sodium chloride will be administered to patients in the tirofiban group, and patients in the heparin group will receive an infusion of 0.9% sodium chloride via micropump. Only the nurses who prepared the fluids will know which are genuine medications. Once heparin or tirofiban stop at 24 h, DAPT will be initiated the next day of surgery and continued daily (ticagrelor 90 mg twice daily plus aspirin 100 mg daily in patients with platelet count ≥ 9 × 10^9^ cells/L; aspirin alone daily in patients with platelet count < 9 × 10^9^ cells/L). For patients who are unable to be extubated within 24 h, heparin or tirofiban will be continued until the patient is extubated, at which point DAPT will start. The timeline of antithrombotic drugs is showed in Fig. 2.

**Fig. 2 Fig2:**
[figure not shown]
Timeline of antithrombotic drugs. DAPT, dual antiplatelet therapies

To ensure patient safety, heparin and tirofiban doses will be adjusted according to routine blood and coagulation parameters obtained 4 and 10 h after treatment initiation. If the platelet count is < 90,000/mm^3^ after a repeat test, tirofiban infusion will be discontinued. If the activated partial thromboplastin time increases to 2.5 to 3 times the normal upper limit value, the heparin or tirofiban dose will be halved; if more than 3 times, they will be discontinued. If the fibrinogen level decreases to < 1.0 g/L, heparin and tirofiban infusions will be discontinued and fresh frozen plasma will be administered.

### Criteria for discontinuing or modifying allocated interventions {11b}

Participants may leave the experiment at any time for any reason as required by the Declaration of Helsinki. Although there are no particular withdrawal requirements, researchers can withdraw patients as necessary and note the cause. All participants will be followed for clinical outcomes unless permission is expressly revoked.

Pregnant women will be excluded. Menstrual history and human chorionic gonadotropin level will be examined in non-menopausal women. Pregnancy after enrollment will not be regarded as an adverse event or significant adverse event (SAE) in and of itself and will not be considered grounds for study exclusion; however, the patient will be given the opportunity to withdraw if she wishes.

During each study visit, patient safety will be addressed. Participants will receive information regarding who to contact in case of a SAE. Those who experience a SAE will be counseled to withdraw.

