### Procedure for unblinding if needed {17b}

The DSMB will periodically examine all safety and outcomes data. Appropriate information regarding adverse occurrences will be systematically gathered and presented to regulatory authorities.

Emergency unblinding will be performed only when necessary for subject safety. Only those individuals who are required to know treatment allocation will be given this information in such an event. If medically appropriate, all subjects will resume the study treatment after recovery and continue to do so until the end of the study.

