### Methods in analysis to handle protocol non-adherence and any statistical methods to handle missing data {20c}

The analyses will not include participants who were randomly assigned but later determined to be ineligible. Additional types of non-compliance that can be identified from the research data, such as visits outside of predetermined times, will be evaluated and classified as significant or minor. Similarly, protocol violations will be rated as significant or minor. After participants with significant procedure violations are eliminated, sensitivity analyses will be conducted. Missing data will not be imputed for these analyses.

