### Adverse event reporting and harms {22}

Complete information regarding all SAEs (nature of the event, start and end dates, severity, link to the trial and/or trial protocols, and outcome) shall be noted in the medical record and eCRF within 24 h of occurrence. Such incidents will be followed up until satisfactorily resolved and stabilized. With reference to the study protocol and Reference Safety Information, the site principal investigator will utilize medical judgment to assess seriousness, causation, severity, and expectedness. The site team and main investigator will determine the relatedness and expectedness. According to the study protocol, the sponsor will validate data collection and SAEs. The sponsor will report safety information to the chief investigator or a delegate for ongoing risk/benefit assessment and collaborate with the chief investigator to submit an annual safety report to the research ethics committee until the end of the study, when an end of study form will be submitted.

The trial steering committee will assess safety in line with a predefined charter, reviewing recruiting and the overall status of the trial on a regular basis; it will also interact with the sponsor regarding safety problems. A relevant unexpected SAE will be reported to the sponsor, who will then notify the ethics committee. The study data center will offer an eCRF for central data collection of adverse events and SAEs which will be submitted to the trial steering committee every 6 months until the study is completed.

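### Counselling every patient with an SAE to withdraw, without separating study drug from follow-up, invites outcome-dependent loss before the 30-day MACCE endpoint

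*Protocol article*

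**What the plan says.** Section {11b} of the protocol article contains three statements on leaving the trial.

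- On withdrawal in general: "Although there are no particular withdrawal requirements, researchers can withdraw patients as necessary and note the cause".
- On follow-up, in the next sentence: "All participants will be followed for clinical outcomes unless permission is expressly revoked".
- On serious events, at the end of the section: "Those who experience a SAE will be counseled to withdraw".

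Other sections bear on the same patients.

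- The text after Figure 1, under Randomization and intervention, has DAPT begin after study drug ends: "Once heparin or tirofiban stop at 24 h". Patients not extubated by then stay on study drug until extubation.
- Procedure for unblinding {17b}: "If medically appropriate, all subjects will resume the study treatment after recovery and continue to do so until the end of the study".
- Adverse event reporting {22}, on SAEs: "Such incidents will be followed up until satisfactorily resolved and stabilized".
- Section {20c}, after a sentence on sensitivity analyses: "Missing data will not be imputed for these analyses".

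The primary efficacy outcome is MACCE to 30 days (Outcomes {12}), compared by a chi-square or Fisher test ({20a}). TIMI major bleeding is also counted to 30 days.

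**The concern.** The last sentence of {11b} tells staff to urge one group of patients towards withdrawal, and that group is defined by having done badly. It is stronger than the wording used in the same section for pregnancy, where the participant is only offered the chance to leave.

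The sentence does not say what is being withdrawn from. Once study drug has ended there is no drug left to stop, so for most of the 30 days it can act only on follow-up. Patients are then being steered towards revoked permission, the only exception that {11b} allows to following everyone.

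If sites act on it, 30-day outcomes go missing in patients with a worse prognosis. If one drug causes more bleeding or other SAEs, more go missing in that arm, and a comparison of observed patients flatters it. Later MACCE components, TIMI major bleeding and kidney injury in those patients would be lost too. An analysis plan cannot recover outcomes that were never collected.

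**Working it through.** **1. What withdrawal can mean, by timing of the SAE**

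| Time of SAE | Study drug | What withdrawal can act on |
|---|---|---|
| Before 24 h (or extubation, if later) | Running | Drug, follow-up or both; the text does not say |
| After that, to day 30 | Ended | Follow-up only |

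Section {11b} opens with participants leaving the experiment and uses withdrawal in that sense for pregnancy. Nothing in it limits the SAE sentence to study drug.

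**2. The plan's own figures**

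Sample size {14} gives 40% MACCE on heparin, a 25% reduction described as absolute, two-sided alpha 5% (sidedness from the Discussion), power 80%, and 712 described as per group. With 40% vs 30% (25% read as relative) and average rate 0.35:

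n per group = [1.960 × √(2 × 0.35 × 0.65) + 0.842 × √(0.40 × 0.60 + 0.30 × 0.70)]² / 0.10² = 356, so 712 in total.

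The literal reading, 40% vs 15%, gives 49 per group (98 in total). The 10-point effect and the loss allowance used below (730 − 712 = 18, or 18/730 = 2.5%) therefore rest on reading 25% as relative and 712 as the total.

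**3. Illustration of the bias**

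The documents give no SAE rate and no withdrawal uptake, so every input here is assumed. Let s be the share of an arm with a non-MACCE SAE and w the share of those who withdraw. MACCE risk is 60% after such an SAE and 30% otherwise, and no MACCE is recorded in those who withdraw.

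- True risk = (1 − s) × 0.30 + s × 0.60
- Observed risk = [(1 − s) × 0.30 + s × (1 − w) × 0.60] / (1 − s × w)
- Shift in the risk difference = (true − observed) in the arm with more SAEs, minus the same quantity in the other arm

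Middle case, s = 20% vs 10%, w = 50%:

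- Arm with more SAEs: true 0.24 + 0.12 = 36.0%; observed (0.24 + 0.06)/0.90 = 33.3%; understated by 2.67 points.
- Other arm: true 0.27 + 0.06 = 33.0%; observed (0.27 + 0.03)/0.95 = 31.6%; understated by 1.42 points.
- Shift: 2.67 − 1.42 = 1.25 points.
- Loss: (10% + 5%)/2 = 7.5%, about 55 of 730.

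| SAE share in the two arms | Withdrawing | Understated by (points) | Shift (points) | Lost of 730 |
|---|---|---|---|---|
| 10% vs 5% | 25% | 0.69 vs 0.36 | 0.3 | 14 |
| 20% vs 10% | 50% | 2.67 vs 1.42 | 1.25 | 55 |
| 30% vs 15% | 100% | 9.0 vs 4.5 | 4.5 | 164 |

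With equal s and w in both arms the shift is zero in this model, so the bias needs SAE-related loss to differ by arm.

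**4. Staying inside the allowance is not protection**

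Suppose there is no true effect (40% in both arms of 365), and that in one arm only, 10% of MACCE patients leave before the event is recorded while nobody else leaves. That is 365 × 0.40 × 0.10 ≈ 15 patients, fewer than 18. The observed rate in that arm is 0.40 × 0.90/(1 − 0.04) = 37.5%, a spurious 2.5-point benefit. The two-sided type I error becomes about 10.5%. This is a deliberately unfavourable pattern.

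**The case against.** **A flat contradiction.** A reader might infer that {11b} contradicts itself. The follow-up rule comes directly after the statement that researchers may withdraw patients, so it can be read as covering withdrawn patients too. Being counselled to withdraw is not the same as revoking permission, and the section heading concerns allocated interventions. This stands: it is an unresolved tension. A drug-only reading is strained, however, for SAEs after study drug has ended.

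**Outcomes might still be obtained.** Section {22} follows each SAE until it resolves, and {26b} seeks permission for long-term monitoring of electronic records without patient contact. Both count against treating every withdrawal as a missing outcome. Neither secures day-30 outcomes in a patient who revokes permission, and following one SAE does not capture later events.

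**Conflict with resuming treatment.** A reader might take {17b} as a general rule that patients with an SAE resume treatment. It sits directly after the emergency-unblinding rule and is subject to medical judgement, so it needs reconciling with {11b} but is not clearly opposed to it.

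**No imputation.** A reader might infer that {20c} rules out imputation for the primary analysis. The sentence may refer only to the sensitivity analyses just before it. What can be said is that no imputation is stated for the primary analysis.

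**Loss of MACCE cases themselves.** A patient whose SAE is a MACCE has already met the primary endpoint. The primary comparison is exposed through patients who leave after a non-MACCE SAE; for the others, what is lost is later component and safety events.

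**Assumed size.** Every driver of the bias is assumed, including the 2:1 imbalance between arms. The upper end requires all such patients to leave with no outcome retrieved. This stands in full.

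**Conclusion.** The point holds as a badly fixed instruction. Section {11b} directs staff to counsel patients with an SAE to withdraw, does not separate drug from follow-up, and after study drug ends can act only on follow-up. If followed, it makes loss depend on bad outcomes, and on arm if SAEs differ, in a trial whose primary efficacy endpoint runs to day 30.

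The size is not derivable from the documents. Under the assumed ranges the MACCE risk difference moves by about 0.3 to 4.5 percentage points in favour of the arm with more SAEs. The comparison with a 10-point design effect and an allowance of 18 of 730 depends on the reinterpretation of the sample size section shown above.

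Confidence is high that the sentence is ambiguous and steers patients the wrong way for outcome ascertainment, and much lower on how much bias would follow. It should be fixed; the documents do not show that the primary result would be invalid without the fix.

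**What to change.** Replace the SAE sentence in {11b} with: *Participants with an SAE remain in outcome follow-up to day 30 unless they themselves withdraw consent; stopping study drug is not withdrawal from the study.*

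Reconcile {11b} with {17b} and {22} so that they agree on what happens to study drug and to follow-up after an SAE. What the clinical rule on study drug should be is for the investigators; none is proposed here.

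The cost is one sentence in the protocol, submitted as an amendment under {25}, and a note to sites. Weekly contact for 30 days is already planned ({30}), and the sample size does not change.

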### Strategies to improve adherence to interventions {11c}

Three strategies to improve subject adherence to interventions will be implemented. First, a portion of the individuals’ health care and travel expenditures will be reimbursed. Second, physicians will offer free consultations. Finally, the researchers will communicate with the subjects at least once a week.

### Relevant concomitant care permitted or prohibited during the trial {11d}

Standard secondary CAD prevention measures will be implemented. Oral beta-blockers will be used before and after surgery to maintain heart rate between 60 and 80 beats per minute. To maintain low density lipoprotein concentration below 1.88 mol/L, an oral statin or combination of lipid-lowering medications will be prescribed. All episodes of care will be recorded in an electronic case report form (eCRF).

### Provisions for post-trial care {30}

Patients will be contacted every week in 30 days and once a year after trial to monitor for adverse effects, provide encouragement and motivation, answer questions, and assist with any problems.

### Outcomes {12}

#### Primary outcomes

The primary safety outcome (phase I) is total chest tube drainage output over 24 h. The primary efficacy outcome (phase II) is incidence of MACCEs in the first 30 days after surgery.

### Definitions

All-cause death is defined as death from any cause. POMI is defined as MI within 48 h of CABG. MI is defined according to the fourth universal definition of MI: cardiac troponin concentration > 10 times the 99th percentile upper reference limit or > 20% increase in cardiac troponin concentration plus new pathologic Q waves on electrocardiography, graft occlusion on angiography, or new abnormal segmental ventricular wall motion on echocardiography. MI more than 48 h after surgery is defined as cardiac troponin concentration above the 99th percentile upper reference limit and at least one of the following: (1) new ischemia or new pathologic Q waves on electrocardiography, (2) imaging of new loss of viable myocardium or new regional wall motion abnormality in a pattern consistent with an ischemic cause, and (3) identification of a coronary thrombus on angiography [26].

All patients with stroke symptoms will be examined to rule out conditions that mimic stroke (e.g., seizure, conversion or somatoform disorder, migraine headache, and hypoglycemia) and then undergo urgent computed tomography and/or magnetic resonance imaging to confirm the diagnosis. Acute ischemic stroke is defined as a new neurologic deficit lasting more than 24 h in conjunction with imaging findings of cerebral infarction. Early revascularization is defined as any percutaneous or surgical revascularization performed for graft failure or ACS resulting from a lesion inside or adjacent to a graft within 30 days. Acute postoperative kidney injury is defined according to the Society of Thoracic Surgeons as the following: (1) serum creatinine ≥ 2 0.0 mg/dL or increase to twice the preoperative baseline concentration or (2) new requirement for dialysis [27].

### Participant timeline {13}

The participant timeline is shown in Table 2.

**Table 2 Tab2:**
[figure not shown]
Schedule of enrolment, interventions and assessments

*ECG* Electrocardiogram, *UCG* echocardiography, *UDPB* Universal Definition for Perioperative Bleeding, *TIMI* Thrombolysis in Myocardial Infarction, *MACCE* Major adverse cardiovascular and cerebrovascular events, *AK*
*I* Acute kidney injury

### Recruitment {15}

The average number of annual CE-CABG procedures over the past three years at Anzhen hospital was approximately 600. Combined with the other two centers, achieving the required number of participants is feasible.

## Assignment of interventions: allocation

### Sequence generation {16a}

All eligible subjects will be allocated by clinical staff to either heparin group or tirofiban group in a 1:1 ratio at 2 h after CE-CABG using an interactive web response system (IWRS). A static randomization list is generated and implemented within the system which accounted for three strata: study site, patient age group (< 70, ≥ 70 years) and gender group (male, female) using the biased-coin minimization method. Each center will have a designated user of the interactive system. This user will generate a random sequence for patients who meet criteria for enrollment and communicate the allocation to the research nurse.

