### Randomization and intervention

Eligible patients will be randomized to either the heparin or tirofiban group in a 1:1 ratio utilizing an interactive online response system. Using the biased-coin minimization approach, a static randomization list will be created and applied taking three strata into consideration: research site, patient age group (< 70 and ≥ 70 years), and gender. Figure 1 depicts the enrollment and randomization procedures.

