### Concealment mechanism {16b}

The random sequence will be immediately sent to a designated nurse who prepare the fluids and medications. For the tirofiban group, a 50-mL volume of tirofiban fluid and a 5-mL volume of 0.9% sodium chloride (labeled as heparin) will be prepared. For the heparin group, a heparin fluid and a 50-mL 0.9% sodium chloride (labeled as tirofiban) will be prepared.

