### Implementation {16c}

Doctors and nurses working near the bed will have no idea which fluid is genuine medication. These fluids will be infused according their label names. Thus, all subjects, site staff, sponsor staff, assessors, and data analysts will be blinded to randomization outcomes.

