## Assignment of interventions: blinding

### Who will be blinded {17a}

All subjects, site staff, sponsor staff, staff (with exceptions as indicated below), assessors, and data analysts will be blinded to randomization outcomes until the database is unlocked. Exceptions will include (1) nurses who prepare the fluids and medications (heparin, tirofiban, or just 0.9% sodium chloride), (2) computer programmers involved in randomization and drug management processes, and (3) the biostatistician creating reports for the Data and Safety Monitoring Board (DSMB).

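### The site user who passes on each allocation knows every arm at that centre but is missing from the list of unblinded roles, and the randomization wording leaves concealment unsecured

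*Protocol article*

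**What the plan says.** Sequence generation {16a} describes the chain of allocation in four statements:

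- On who allocates: "All eligible subjects will be allocated by clinical staff to either heparin group or tirofiban group in a 1:1 ratio".
- On where the list sits: "A static randomization list is generated and implemented within the system".
- On access: "Each center will have a designated user of the interactive system".
- On what that user does: "This user will generate a random sequence for patients who meet criteria for enrollment and communicate the allocation to the research nurse".

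Concealment mechanism {16b} takes up the next step: "The random sequence will be immediately sent to a designated nurse who prepare the fluids and medications". It then describes how active and dummy fluids are prepared and labelled.

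On blinding, Implementation {16c} concludes that "all subjects, site staff, sponsor staff, assessors, and data analysts will be blinded to randomization outcomes", with no exception. Who will be blinded {17a} repeats this with three exceptions. The first reads "Exceptions will include (1) nurses who prepare the fluids and medications (heparin, tirofiban, or just 0.9% sodium chloride"; the others are the programmers who handle randomization and drug management, and the biostatistician who reports to the DSMB. The text under Fig. 1, in Randomization and intervention, says that nobody but the preparing nurses knows which fluid is active.

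On method, Randomization and intervention states: "Using the biased-coin minimization approach, a static randomization list will be created and applied". The factors are site, age group and sex. Section {16a} gives the same pairing of list and method.

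**The concern.** The article claims blinding of everyone at the site except the preparing nurses, but its own allocation procedure creates a second site role that learns every arm. The text does not say whether that person also enrols patients, works at the bedside, records chest tube drainage or judges endpoints.

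This matters for both phases. Drainage over 24 h is the phase I primary outcome and decides whether phase II starts. In phase II, myocardial infarction and early revascularization depend partly on decisions to investigate or intervene, and knowledge of the arm can influence those decisions.

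A second question follows. Eligibility is settled about 2 h after surgery, immediately before allocation. If the person requesting the assignment could anticipate the next arm and also influenced that decision, selection would be possible. Whether the arm can be anticipated depends on the randomization method, and the article describes that method in terms that do not fit together.

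**Working it through.** **Blinding: who learns the arm, against who is listed as unblinded.** No arithmetic applies, so the sections are set side by side.

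| Site role | Learns the arm? | Listed as unblinded in {17a}? |
|---|---|---|
| Designated system user at each centre ({16a}) | Yes, must know it to pass it on | No |
| Nurse preparing the fluids ({16b}) | Yes | Yes |

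Two site roles learn the arm and one is listed. The user is not the nurse, because the user communicates to the nurse. A centre-level user is not plausibly one of the programmers, and is not the DSMB biostatistician. So {16a} conflicts with three places: the statement in the intervention section that only the preparing nurses know, {16c}, and {17a}.

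**Method: static list against minimization.** Minimization sets the probability of each assignment from the factor levels of patients already entered. It therefore cannot be fixed in advance as a static list. A static list does not respond to earlier patients, so it is not minimization. The two also need different safeguards. A list needs upcoming entries hidden. Minimization also needs past allocations hidden, because they carry information about the next one.

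**How predictable the next arm would be under real-time minimization.** This was checked by simulation.

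Inputs from the article:
- 3 centres (Anzhen and two others), 2 age groups, 2 sexes, 1:1 allocation.
- 266 patients in phase I.

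Inputs assumed, because the article does not give them:
- Site shares 60/20/20.
- Age and sex each split 75/25.
- Coin probability p of 0.7, 0.8 or 0.9 in favour of the arm that reduces marginal imbalance.

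Rule for each new patient: sum the arm imbalances over that patient's site, age group and sex; assign the arm that reduces the sum with probability p; if tied, assign at 0.5. The guesser names the arm that the rule would favour, given what the guesser knows.

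| Coin probability | Correct guesses, own-site history only | Excess over 50% | Correct guesses, history of all three sites |
|---|---|---|---|
| 0.7 | about 59% | 9 points | 68% |
| 0.8 | about 62% | 12 points | 76% |
| 0.9 | about 63% | 13 points | 83% |

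Repeat runs move these figures by a point or two, depending on how imbalance is scored. The own-site column is the relevant one, since {16a} gives each centre its own user and nothing says that a user sees other centres' allocations. It is lower because the age and sex totals that drive the rule are trial-wide, and a local user sees only part of them.

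**The case against.** The strongest reply is that a reader might infer from this that allocation concealment fails, and the article does not support that. Concealment concerns foreknowledge before enrolment. Section {16a} keeps the list inside the web system and has the user act on patients who already meet the criteria. Learning an arm after assignment affects blinding, not concealment. No section says that the list is visible at a site. This stands.

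Three further readings also go too far:

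- **A separate route in {16b}.** That section does not say who sends the allocation or that it goes directly from the system. Sections {16a} and {16b} read naturally as one chain from user to nurse.
- **A user who steers enrolment or judges outcomes.** That the user is one of the clinical staff is a fair inference from neighbouring sentences, but it is not stated. No section gives the user a part in eligibility, care or assessment, and the eligibility thresholds at 2 h are largely objective.
- **Predictability of 68% to 83%.** Those figures require knowledge of every earlier allocation at all three sites, which the article does not give this user.

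It can also be said that the double-dummy preparation protects bedside staff and assessors, and that system permissions and the coin probability usually sit in a fuller document. Both are fair, and the missing coin probability is not held against the article. They do not remove the contradiction, which lies between sentences that the article does print. Nor does it help to read the exceptions in {17a} as merely examples, because {16c} allows none and the intervention section limits the knowledge to the preparing nurses.

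**Conclusion.** The blinding description is wrong as written. One site role at each centre knows every arm allocated there, contrary to three other places in the article, and nothing printed separates that role from enrolment, care or outcome assessment. This rests on the text alone.

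Concealment is not shown to fail, but it is not secured by the wording. Saying that the user generates a sequence leaves open whether more than the current assignment is visible, and a static list made by minimization does not describe one definite method. If real-time minimization is used and the user knows only own-site history, correct guesses of about 59% to 63% against 50% are a reasonable illustration. That range depends on the assumed coin probabilities and on the assumed site, age and sex shares. It measures predictability only. The documents give no basis for a size or direction of bias in drainage or MACCE.

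This should be corrected. It does not show that the double-dummy blinding of bedside staff has broken down.

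**What to change.** 1. In {16a}, have the web system return only a confirmation or participant number to the requesting user, and release the arm solely to the nurse who prepares the fluids. Say the same in {16b}.
2. If the user must see the arm, add that role to the exceptions in {17a} and bar it from eligibility decisions, bedside care, drainage recording and outcome assessment.
3. Replace the wording about generating a sequence with a request for one assignment per patient of confirmed eligibility, with upcoming assignments hidden.
4. Name one method in both Randomization and intervention and {16a}: either real-time minimization with a random element, or a concealed stratified list.
5. Align the intervention section, {16a}, {16b}, {16c} and {17a} so that they name the same unblinded roles.

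The cost is a permission setting in the system and a few sentences. The first option needs no extra staff. The second requires each centre to keep its system user out of the listed tasks. The trial is already recruiting, so the text should describe what the system actually does; any change in practice would go through the amendment route that the article sets out.
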